**Figure 4 Fig4:**
[figure not shown]
**inSCALE conceptual framework.**

The community engagement approach aims to enhance the perceived value of the CHW, both for themselves and for the communities they serve, through inclusive and participatory local activities. The actions of health club members will help communicate to the CHW and village members that their work is important, of value and appreciated. In doing so, village health clubs (VHCs) will improve the status and standing of CHWs as key village health assets, increasing their motivation and the quality of service provision. VHCs will also increase the community’s understanding of what CHWs can and cannot do and their potential to improve child health in the village. This increased understanding could mean that a greater demand for CHW services and, correspondingly, an increase in the number of children accessing them. The training of CHWs to facilitate the health clubs will reinforce and add to skills acquired during iCCM training and may also improve quality of care. VHCs will hopefully become valued forums, increasing the capacity of both the CHW and the village inhabitants to address health issues in their communities and ensure children are receiving timely, effective and appropriate treatment.

There is also a possibility that both interventions could lead to substantial engagement of community members with child health issues, over and beyond what could be reasonably attributed to their relationship with CHWs. In this scenario, improved care-seeking will not only be due to increased CHW motivation and retention, but also to enhanced community knowledge and action for child health. This process will be captured through the alternative mechanism outlined in Figure 4.

### Overview of trial design

The inSCALE interventions are being evaluated through cluster randomised controlled trials (cRCTs) in Uganda and Mozambique. The clusters are sub-counties in Uganda and districts in Mozambique, and correspond to the lowest administrative units where CHW services are coordinated, with an average of 60 VHTs and 18 to 25 APEs per cluster, respectively. In Uganda, there are 95 clusters in the eight study districts. In order to be eligible for randomisation, a cluster had to have CHWs trained in iCCM by 31 January 2011 (3 months before starting the baseline survey). Clusters that had less than ten villages or that were participating in another Malaria Consortium mobile phone pilot study were excluded. Overall 41/95 clusters were eligible for randomisation. In Uganda, the trial consists of a three-arm cRCT with 13 clusters in each arm; two clusters were not randomised and were designated as spare/back-up clusters in case of the need to drop one of the selected 39. In Mozambique, there are 12 clusters, allowing a two-arm cRCT.

The trial planning started in April 2011, and the inSCALE interventions were developed and fully implemented in the intervention areas by the end of 2012 in Uganda and by the end of June 2013 in Mozambique. Impact data on the main outcomes was collected in an end-line household survey after 12 months of implementation in Uganda (March-May 2014) and will be collected after 18 months of implementation in Mozambique (February 2015). Detailed process, cost and cost-effectiveness evaluations are being carried out in both countries. All data collection is expected to be completed in May 2015, and results will be available by the later part of 2015.

### Randomisation

Restricted randomisation was performed to minimise the difference between the intervention and control arms for key indicators of the average proportion of children appropriately treated for fever, diarrhoea, and pneumonia (FDP); VHT motivation (mean); and the mean (log10) cost of treatment for children with FDP [19]. The randomisation of clusters to the three arms was restricted to those randomisation schemes where there were minimal between-arm differences for these five key parameters but still allowed adequate numbers of randomisation schemes, as too few schemes could elicit selection bias [20].

In Mozambique, appropriate treatment for childhood FDP could not be measured reliably at baseline due to a delay in the roll-out of the APE kits containing iCCM medicines. Attempts to seek care from an APE or a public facility were chosen as proxy markers for overall appropriate treatment, as these showed the strongest correlation with appropriate treatment. This was based on an assessment of the relationship between appropriate treatment with these and other candidate variables using parallel data from the Uganda baseline survey (where appropriate treatment was measured), and by assessment of the cluster averages and variances for several care seeking variables from the Mozambique dataset itself.

In Uganda, out of 500,000 random allocations of 39 clusters to three arms, 13,683 of the allocations fit all criteria. After applying a further filter to ensure that all districts had at least one sub-county in the mHealth intervention arm, and that at least the larger districts had a control arm, a final scheme was picked from the resulting sub-sample of 1,791 allocation schemes. In this scheme, all districts had at least one sub-county in the control arm and one in the mHealth intervention arm, and five out of eight districts also had at least one sub-county in the participatory community engagement arm (Figure 5).

**Figure 5 Fig5:**
[figure not shown]
**Interventions and control arm clusters in Uganda.**

Within Mozambique, there were 924 possible unique ways to sort 12 districts into two groups. In total, 84 schemes from these potential 924 met the all restriction criteria. A scheme was picked at random from the final 84 schemes, and was thus the final chosen scheme for the Mozambique study (Figure 6). In both sites, the selected schemes had no more than a 5% (proportions) or a 0.5 (scores/counts) difference between arms for any parameter. Sorting of clusters and random selection of schemes were carried out in Stata v12.1 (StataCorp, Texas USA).

**Figure 6 Fig6:**
[figure not shown]
**Intervention and control arm clusters in Mozambique.**

### Intervention areas

The inSCALE interventions as described above were implemented in the 26 sub-counties in Uganda (13 in the ‘mHealth intervention arm’ and 13 in the ‘community engagement intervention arm’) and in six districts in Mozambique. All CHWs and children living in these clusters were potential recipients of the CHW intervention, in addition to having access to routine care currently available from private and public health services.

### Control areas

Children living in the control areas continued to benefit from the routine Ministry of Health iCCM package provided by the CHWs who were supported by the national and sub-national health services with funding from Malaria Consortium’s CIDA-iCCM project.

### Sample size

The sample size calculations, which are based on a cluster RCT with 13 and 6 clusters per arm in Uganda and Mozambique, respectively, are based on the main evaluation outcome: the percentage of children receiving appropriate treatment during illness episodes for each of pneumonia, diarrhoea and fever. This is also the outcome that requires the largest samples, as not all children surveyed will have had a recent illness episode. Inter-cluster coefficients of variation, baseline appropriate treatment rates, and prevalences of illness were calculated from data collected during the baseline surveys in each site and used in the sample size calculations (assuming a 5% significance level).

The calculation was based on the formula for comparison of proportions, adjusted for cluster effects stated in equation 7.7 of Hayes and Moulton [21], that is, where k is the between cluster coefficient of variation:$$ C = 1 + \left(\mathrm{z}\upalpha /2 + \mathrm{z}\upbeta \right)2\left(\ \left(\uppi 0\left(1\ \hbox{--}\ \uppi 0\right)/\mathrm{m} + \uppi 1\left(1\ \hbox{--}\ \uppi 1\right)/\mathrm{m} + \mathrm{k}2\left(\ \uppi 02 + \uppi 12\right)\right)\ /\left(\uppi 0\ \hbox{--}\ \uppi 1\right)2\ \right) $$

The number of sick children required/cluster was determined by varying this number in the formula for the number of clusters until the number of clusters/arm equals 13 and 6, respectively [21]. Thus, sampling 155 children per cluster in Uganda would yield enough sick children to have 90% power to detect a 15% difference in the appropriate treatment of pneumonia and fever and a 20% difference in diarrhoea between arms. Sampling 390 children per cluster in Mozambique would yield enough sick children to have 90% power to detect 20% and 25% differences in appropriate treatment of fever and pneumonia respectively, and 80% power to detect a 25% difference in appropriate treatment of diarrhoea between arms.

The sample size formula and sampling scheme were also used to inform the design of the baseline surveys (which involved surveillance of households, CHWs and health facilities). At baseline, site-specific data was not available for k; therefore, a conservative estimate of 0.15 was used to inform the baseline sample size calculations in both sites. Prevalence values for FDP in the sites were based on estimates from recent Demographic and Health Surveys [22,23], Malaria Indicator Surveys [24,25], and in the case of Mozambique, an Integrated Health Systems and Child Friendly District Survey by UNICEF [26]. In Uganda, 3,900 households with children under the age of 5 years were sampled at baseline; of the 6,501 children in these households, 47% were reported as having had symptoms of fever, 11% with diarrhoea and 24% with pneumonia in the two weeks prior to the survey and were thus eligible for the full household survey questionnaire on treatment, care seeking, and health practices. In addition, 360 VHTs and the 79 health facilities supporting these VHTs were also sampled as part of the baseline. In Mozambique, 2,970 households with children under the age of 5 years were sampled; of the 4,422 children in these households, 29.2% were reported as having had symptoms of fever, 5.2% with diarrhoea and 10.7% with pneumonia in the two weeks prior to the survey. Data were also collected from 256 iCCM-trained APEs and the 80 health facilities to which they reported.

### Impact evaluation

The primary outcome is the change in carer reported appropriate treatment for fever, diarrhoea and pneumonia in children in households receiving the intervention(s) compared to those in areas with routine iCCM (‘control’ households). A proportion of children will have had two or more conditions simultaneously. We intend to group all conditions and assess the ‘use of appropriate drugs for this episode of illness for all illness episodes by intervention arm. Additionally, the effect of the interventions on appropriate treatment for each of the three conditions individually will be established as a way of understanding the pathways through which the interventions worked. The main comparison for effect will be obtained from the measured difference between interventions and control arms at end-line. Baseline characteristics were used to perform restricted randomisation to minimise the difference between the intervention and control arms on key indicators.

Secondary outcomes include a number of performance, retention, motivation, access and cost-effectiveness outcomes:Mean motivation score (motivation outcome)% CHWs staying in post after 1 year of implementation (retention outcome)% monthly reports complete and submitted on time (performance outcome)% CHWs with medicine stock-out <1 week each quarter (performance outcome)% caregivers with sick child in the last 2 weeks who accessed iCCM treatment (coverage outcome)% caregivers willing to use CHWs (access outcome)% of start-up costs compared to recurring costs of the intervention packages (cost outcome)Cost per CHW trained (cost outcome)% of start-up costs compared to recurring costs of the intervention packages (cost outcome)Cost per child who receives appropriate treatment for each of diarrhoea, pneumonia and fever (cost-effectiveness outcome)Cost per episode of illness treated correctly (cost-effectiveness outcome)Cost- per life year gained (LYG) and DALY averted (cost-effectiveness outcome)

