**Details of inSCALE’s two integrated intervention packages.**

#### Intervention package 1 - The participatory community engagement approach

In Uganda, the inSCALE project is supporting the implementation of an innovative participatory community engagement approach called the Village Health Clubs (VHCs). The VHC aims to improve child health through a community-led forum with the CHWs as the main focus point. VHC meetings are intended to provide a forum where CHWs and community members who are part of the club can work together to identify child health and CHWs challenges. They use village networks, knowledge, creativity and other community assets to help solve child health problems. Village health clubs are implemented through a four-step learning, planning and action cycle facilitated by the CHW. The time between each step is 1, 2 or 4 weeks depending on the decision taken by the club members. Health club members rank child health challenges faced by their community using picture cards. They discuss solutions, which include supporting the functioning of CHW services, and take actions to meet these challenges. Throughout the cycle the health clubs monitor and report on their progress.

Village health clubs are open to all members of the village and designed to be fun while focusing on the CHW as the main village health asset. A participatory empowerment approach is adopted where the CHW (as facilitator) encourages members to plan and carry out the club’s activities. They also promote group decision-making and ownership. Solutions to village health challenges developed by village members are a key focus of the village health club approach. Table 1 describes the contents of the participatory community engagement intervention in Uganda.

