#### Household, CHWs and health facility surveys

The primary outcome in both sites will be collected using an end-line household survey administered to the child’s primary carer. Data will be collected on illness prevalence, proportion of children who have received appropriate treatment and on household socio-economic status. Secondary outcomes, such as CHW performance, will be assessed in a sample of CHWs using a structured questionnaire with pre-tested case scenarios and knowledge questions administered by a trained research assistant. A motivation tool has been developed and validated to establish a composite index of CHW motivation. A health facility questionnaire will be used to collect data from health facility staff/supervisors on CHW supervision, support and health system costs.

The quantitative survey questionnaires will be adopted from the tools used for the baseline survey. These were developed in an iterative process: i) with the team of researchers in London and Kampala/Mozambique, ii) with potential field supervisors, and finally, iii) with trainees of the data collector training. Both the field supervisors and data collectors will visit local homes under supervision of a researcher to practice and test the questions and make revisions. All questionnaires will be written in English and translated into the local languages (Runyoro, Luo and Luganda for Uganda and Portuguese for Mozambique), and the accuracy of the translation will be checked by back translation into English. Key illness terminologies and other sensitive expressions will be translated into the native languages during the training and provided to the research assistants on a hard copy which guided them during the interview. Field editing will be done for consistency and completeness and after correction, data will be double-entered by trained data entry clerks into a SQL data management system capable of consistency, range, inter-database checks and audit trails.

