The lack of an accurate measurement to estimate coverage of appropriate treatment of sick children is one weakness of the study. Coverage of maternal, neonatal and child health (MNCH) interventions are typically monitored through household surveys, which estimate treatment rates based on 2-week recall of illness symptoms by caregivers. However, these survey tools identify children with reported symptoms, and for illnesses like pneumonia where the true prevalence in community settings is low, this methodology does not provide an accurate denominator of cases for monitoring treatment rates [29]. Issues with recall of diagnostic results and treatments provided have also been documented [30,31]. While we are aware of these limitations, we attempted to increase the validity of our estimates by increasing the recall period to 4 weeks to increase the number of recent cases detected in the survey, and including an expanded list of symptoms indicative of pneumonia in order to increase the specificity of the pneumonia case definition. We also used drug charts to increase the validity of reported treatments. Another possible weakness of the study is the lack of control over contextual factors and other changes in the health system in which the innovations are implemented. While this was anticipated and attempts are made to access district and provincial operational plans and internal project reports, lack of data on factors that may mediate the effect of the interventions [32], such as drug stock-outs, health staff rotation, and concurrent programme implementation by other partners, leaves us unable to plot these influences with absolute confidence in their accuracy.

If evidence yields support for cost-effective innovations that can generate a highly motivated and well-performing workforce of CHWs, there is potential for sustainable coverage of high quality iCCM at scale and significant reductions in child morbidity and mortality.

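### The primary outcome's denominator is illness reported by carers after randomisation, and the article does not consider that it may differ by arm

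*Protocol article*

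**What the plan says.** Under Impact evaluation the protocol article states: "The primary outcome is the change in carer reported appropriate treatment for fever, diarrhoea and pneumonia in children in households receiving the intervention(s", set against areas with routine iCCM. The three conditions are pooled, and use of appropriate drugs is assessed "for all illness episodes by intervention arm". Each condition is also analysed separately, to understand pathways. On timing: "The main comparison for effect will be obtained from the measured difference between interventions and control arms at end-line".

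Under Household, CHWs and health facility surveys: "The primary outcome in both sites will be collected using an end-line household survey administered to the child", the respondent being the primary carer. Illness prevalence is collected in the same survey. The Discussion says of such tools that "these survey tools identify children with reported symptoms", and that for illnesses such as pneumonia "this methodology does not provide an accurate denominator of cases for monitoring treatment rates". It lists three measures taken: a longer recall period, a wider list of pneumonia symptoms and drug charts.

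On the intervention side, the clubs are open to the whole village, and "Health club members rank child health challenges faced by their community using picture cards". The section on effect pathways raises the possibility, for both interventions, of community engagement beyond the CHW relationship. In that scenario "improved care-seeking will not only be due to increased CHW motivation and retention, but also to enhanced community knowledge and action for child health".

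**The concern.** A child enters the primary outcome only if the carer reports symptoms, and the report is made after the intervention has run. Randomisation makes all surveyed children comparable between arms. It does not do so for a subset picked out by a report that the intervention may itself influence.

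The authors' own alternative pathway supplies a reason why it might. Communities that think and act more on child health may notice and report more mild episodes, or may have fewer episodes. Either would change the mix of children in the denominator, and the proportion could move although no given sick child is treated differently. A real gain could be hidden or a false one produced.

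The protections in the article do not reach this. Restricted randomisation and adjustment for baseline imbalance act on differences present before the intervention. The three measures in the Discussion are described without reference to arm.

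There is a second consequence. The cost-effectiveness analysis rests on the number of sick children appropriately treated, and that number can rise while the primary proportion falls.

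**Working it through.** **The plan's own figure.** The sample size section gives 155 children per Ugandan cluster, 13 clusters per arm and 90% power for a 15-point difference in fever and pneumonia. With 155 × 0.47 ≈ 73 fever episodes per cluster and a coefficient of variation k = 0.15 (the article's value for the baseline survey), the stated formula gives power of 0.94 at a control rate of 50% and 0.89 at 60%. The stated 90% is attainable. It cannot be confirmed, because the control rates and the end-line k are not printed. No printed number is in dispute here.

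**Inputs for the illustration.**
- From the article: reported prevalence at the Uganda baseline of 47% fever, 11% diarrhoea and 24% pneumonia, on two-week recall.
- Assumed: 50% of reported episodes treated appropriately; 5 points of extra reported episodes in the intervention arm; 20% of those extra episodes treated; no true effect; one episode per child.

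**Formula.** With prevalence P, treated proportion p, and E points of extra reports treated at rate q, the observed proportion is (P·p + E·q)/(P + E).

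| Case | Calculation | Observed | Shift from 50% |
|---|---|---|---|
| Any illness, P = 47% (fever as floor) | (0.235 + 0.010)/0.52 | 47.1% | -2.9 points |
| Any illness, P = 82% (47 + 11 + 24, no overlap) | (0.410 + 0.010)/0.87 | 48.3% | -1.7 points |
| Pneumonia alone, P = 24% | (0.120 + 0.010)/0.29 | 44.8% | -5.2 points |
| P = 47%, 2 extra points | (0.235 + 0.004)/0.49 | 48.8% | -1.2 points |
| Pneumonia alone, 2 extra points | (0.120 + 0.004)/0.26 | 47.7% | -2.3 points |
| P = 47%, 5 extra points treated at 50% | (0.235 + 0.025)/0.52 | 50.0% | 0 |

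In the first row, treated children per 100 surveyed go from 23.5 to 24.5 while the proportion falls. For pneumonia they go from 12 to 13.

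**The other direction.** If a fraction x of episodes, all untreated, goes unreported or does not occur, the proportion becomes p/(1 - x). At p = 40%, x = 10% gives 44.4% (+4.4 points) and x = 20% gives 50% (+10 points).

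**Effect on the test.** Take the first row with k = 0.15, m ≈ 73 in control and 155 × 0.52 ≈ 81 in the intervention arm, and 13 - 1 = 12 in the divisor, as in the plan's formula. The variance is [0.25/73 + 0.249/81 + 0.0225 × (0.25 + 0.222)]/12 ≈ 0.00143, so the standard error is about 3.8 points. A shift of 2.9 points is then called significant about 12% of the time instead of 5%.

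**Limits of a prevalence test.** For a 10% relative rise in reported fever (47% to 51.7%, 155 children per cluster), the same formula gives power of about 0.28 at k = 0.15 and 0.69 at k = 0.05; k for prevalence is assumed.

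**The case against.** The strongest reply is that this is an omission, not an error. The outcome definition stays as it is, and a prevalence table by arm is the sort of detail that a full protocol or SAP, not shown here, may contain. That limits the point but does not remove it. The article itself fixes the measure, the respondent and the end-line comparison, and the vulnerability lies in that combination. It also discusses the denominator's weakness without raising differences by arm.

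Several stronger readings are tempting, and the documents do not support them.

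- A reader might infer that the club arm is designed to change what carers know about illness. The stated aims are the status of CHWs, understanding of what they can do, demand for their services and local capacity. The wider knowledge route is called a possibility, is ascribed to both interventions, and is linked to care-seeking, not to symptom reporting.
- A reader might infer that the Discussion takes the denominator error to be equal across arms. It is silent on arms. The wider symptom list is meant to improve specificity for pneumonia, which bears in part on spurious reports.
- A reader might take -5.2 points as the bias in the primary outcome. It applies to pneumonia alone, which is a pathway analysis. The pooled outcome has a larger denominator, so the same assumptions give -2.9 points or less.

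It is also fair that the treatment rates and extra reports are assumed, and that baseline prevalence need not describe an end-line survey with longer recall.

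**Conclusion.** The point stands as a risk to validity in a stated measure. It is not a demonstrated bias. Nothing in the article shows that reporting did differ by arm, and the direction could go either way: extra mild, untreated reports dilute an effect, while fewer untreated reports inflate it.

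Under the stated assumptions the pooled proportion moves by about -2.9 points with fever's 47% as a floor for any illness, and by -1.7 points if the three conditions never overlap. Pneumonia alone moves by -5.2 points, about a third of the 15-point difference for which that condition is sized (5.2/15 = 35%). With the same treatment rate among extra episodes there is no shift. The concern covers every intervention-control comparison in both countries, and is most direct for the Ugandan clubs.

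A reader might go further and hold that a coverage claim should be allowed only if the per-child analysis agrees in direction or prevalence does not differ significantly. That does not follow. Suppose 40% are ill and 50% of them treated in control, against 30% ill and 60% treated with clubs. Treated children per 100 fall from 20 to 18, untreated ill children fall from 20 to 12, and the primary proportion improves. Agreement in direction has no clear meaning there. A non-significant prevalence test with power near 0.28 gives little reassurance either.

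**What to change.** Keep the primary outcome. For every intervention-control comparison in Uganda and Mozambique, specify:

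1. The cluster-level difference between arms, with confidence interval, in the reported prevalence of fever, diarrhoea, pneumonia and any of the three, among all surveyed children.
2. A supporting analysis with all surveyed children as denominator, giving separately the proportion ill and appropriately treated and the proportion ill and not appropriately treated.

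State that the primary result will be interpreted beside these estimates, and that the per-child measures also reflect any change in true incidence. Judge the prevalence difference by its estimate and interval. Do not make the coverage claim depend on agreement in direction or on a non-significant prevalence test.

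No new data should be needed. End-line illness prevalence is already to be collected, and the baseline survey, whose questionnaires are to be adapted for end-line, counted all children under five in sampled households. The cost is a little more analysis, and a more cautious reading if prevalence differs by arm.
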